**Fig. 4 f0020:**
[figure not shown]
**RescQ™ pilot progression criteria for feasibility and acceptability**. Red-Amber–Green progression criteria for the two key feasibility outcomes in the RescQ™ pilot: incident-level ambulance clinician uptake and website access among registered bystanders. The thresholds were designed to assess feasibility and acceptability of the pathway rather than clinical effectiveness. **OHCA:** out-of-hospital cardiac arrest; **RAG** = red–amber–green. (For interpretation of the references to colour in this figure legend, the reader is referred to the web version of this article.)

**Table 3 t0015:** RAG progression criteria for feasibility assessment (OHCA: out-of-hospital cardiac arrest).

**Feasibility domain**	**Green**	**Amber**	**Red**
Incident-level paramedic uptake: eligible OHCA incidents with ≥1 bystander registered	≥40%	30–39%	<30%
Website uptake: registered bystanders accessing website at least once	≥90%	80–89%	<80%

#### Secondary outcomes

1.Documentation of the number of bystanders <18 years•Enabling exploratory description of a group whose exposure to OHCA events is not currently known or captured by any reporting system.2.Digital engagement and utilisation•Time from OHCA to first website access for the bystanders seeking LO support.•Frequency and depth of engagement (sessions, time spent, resources viewed).•Types of resources accessed (articles, videos, external links).3.Psychological impact and support outcomes•Change in acute stress (1–10 scale) and validated scores (NSESSS, CORE-10) pre and 2 weeks post LO session.•Self-reported satisfaction with website and LO support.•Perceived usefulness of support in coping with the event.4.Service-delivery and resource use outcomesService-delivery and resource utilisation data will be prospectively collected to assess operational and economic feasibility. Variables will include staff role and grade, time required for on-scene registration and debrief, LO intervention and admin time, supervision and training inputs, platform support, and onward referral activity.

### Subgroup comparisons

Engagement and utilisation will be explored by bystander relationship to the patient (known vs unknown) and age group (including under 18 s), where data are available. Exploratory comparisons will also be made between bystanders who access LO support and those who do not, limited to variables available across the full cohort.

Within the LO subgroup, further descriptive analyses will explore engagement patterns, timing of access, and baseline psychological measures. These analyses are hypothesis-generating in nature.

### Sample size and statistical analysis

As a feasibility pilot, RescQ™ is not powered to evaluate clinical effectiveness. However, two key binary progression criteria will be assessed using pre-specified red-amber-green thresholds: incident-level ambulance clinician uptake and website uptake among registered bystanders (Fig. 4).

For each criterion, the null hypothesis is that the true proportion falls within the red zone, with the design alternative set at the green-zone threshold. Exact one-sided binomial calculations will determine whether the anticipated denominator provides adequate power to reject this threshold. These calculations support feasibility interpretation and progression decisions, not clinical effectiveness testing.

For incident-level ambulance clinician uptake, green will be defined as ≥40% of eligible OHCA incidents having at least one bystander registered, amber as 30–39%, and red as <30%. A denominator of 193 eligible OHCA incidents would provide >90% power to reject a red-zone rate of ≤30%, assuming a true green-zone rate of ≥40%, using a one-sided exact binomial test with *α* = 0.05.

For website uptake, green will be defined as ≥90% of registered bystanders accessing the RescQ™ website at least once, amber as 80–89%, and red as <80%. A denominator of 112 registered bystanders would provide >90% power to reject a red-zone rate of ≤80%, assuming a true green-zone rate of ≥90%, using a one-sided exact binomial test with *α* = 0.05.

Observed proportions will be reported with exact binomial 95% confidence intervals (Clopper–Pearson method), interpreted alongside qualitative feedback, implementation context, and service-delivery data.

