### Intervention (Fig. 1, Fig. 2)

#### Ambulance clinician registration

At the OHCA scene, attending ambulance clinicians provide a brief standardised debrief towards the end of resuscitation, thanking bystanders for their actions, acknowledging potential psychological impact, and offering support through the RescQ™ pilot.

Registration is completed via the RescQ™ app on EEAST iPad devices, which records the event with geo-location and timestamping and generates a unique quick response (QR) code. This can be scanned by other clinicians to register multiple bystanders, or by bystanders themselves to enter their own contact details (email or mobile number). The app also captures whether the bystander is known to the patient and records the number of bystanders under 18 or who decline registration.

Following registration, the bystander’s contact information is transferred immediately to a secure central server and automatically deleted from the ambulance clinician-facing application. Clinicians are therefore unable to access email addresses or mobile telephone numbers after the event has been registered. No additional personal information is stored within the application.

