### Outcomes

#### Primary outcome

The primary outcome is to determine the feasibility of delivering a structured bystander support programme following OHCA using the RescQ™ digital platform.

Feasibility will be assessed across three domains: (i) ambulance clinician uptake (registration of bystanders at the scene), (ii) bystander uptake (accessing RescQ™ website), and (iii) acceptability to both ambulance clinicians and bystanders.

Ambulance clinician uptake will be defined as the proportion of eligible OHCA incidents in which at least one bystander is registered via the RescQ™ app, with ≥40% considered indicative of feasibility.

Bystander uptake will be defined as the proportion of registered bystanders who access the RescQ™ website at least once, with the predefined threshold of ≥90% considered indicative of feasibility.

Acceptability will be assessed using a combination of uptake metrics, structured feedback and free-text responses. Ambulance clinician acceptability is assessed through a feedback questionnaire addressing awareness of RescQ™, ease of using the registration application, perceived suitability of introducing the pathway at scene, perceived burden on clinical workflow and suggestions for improvement (Supplemental Appendix C).

Bystander acceptability is assessed among those accessing liaison officer support using satisfaction ratings for the website and liaison officer intervention, perceived usefulness of support in coping with the event, willingness to recommend the service to others, and free-text feedback. Website access and self-referral rates are also interpreted as pragmatic indicators of acceptability and engagement.

Feasibility and acceptability outcomes will be interpreted using predefined thresholds, summarised in Fig. 4 and Table 3.

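### The 5% error, >90% power and 95% coverage for website uptake are not assured: the methods assume independent bystanders, yet one incident can register several

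*Protocol article*

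**What the plan says.** Under Primary outcome, the unit for the second criterion is the person: "Bystander uptake will be defined as the proportion of registered bystanders who access the RescQ™ website at least once". Under Sample size and statistical analysis, "the null hypothesis is that the true proportion falls within the red zone, with the design alternative set at the green-zone threshold". For website uptake this means 80% against 90%, and the article states "A denominator of 112 registered bystanders would provide >90% power to reject a red-zone rate of ≤80" per cent, "using a one-sided exact binomial test with *α* = 0.05". The same section adds "Observed proportions will be reported with exact binomial 95% confidence intervals (Clopper–Pearson method").

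Under Ambulance clinician registration, the app creates one QR code for each event, and "This can be scanned by other clinicians to register multiple bystanders, or by bystanders themselves to enter their own contact details". The Design section describes consecutive bystanders. No section limits registration to one person per incident, and the first criterion is worded as at least one bystander registered per incident. The article mentions no intra-incident correlation, design effect or clustered interval.

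**The concern.** An exact binomial test and a Clopper–Pearson interval treat the 112 registrants as 112 independent trials. Bystanders registered at one arrest share the crew's explanation and the patient's outcome, and some may share a household (the Introduction says around 70% of arrests happen at home). Positive correlation in whether they open the website is a reasonable expectation, although the article gives no estimate of it.

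Positive correlation inflates the variance of the observed proportion. The red zone is then rejected more often than stated when true uptake is 80%, power at 90% drops, and the interval loses coverage. Website uptake is one of only two formal red-amber-green criteria, and the type I error moves in the permissive direction.

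**Working it through.** **Inputs from the article:** n = 112, p0 = 0.80, p1 = 0.90, one-sided α = 0.05, exact binomial test, Clopper–Pearson 95% interval.

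**Assumptions (not in the article):** registrants per incident and the intra-incident correlation (ICC). For scale, 40% uptake on 193 incidents gives 0.40 × 193 = 77 incidents, and 112 / 77 = 1.45 registrants each. The two denominators come from separate power calculations, so 1.45 is only a working value.

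**Step 1, the plan's own figure.** The critical count r is the smallest with P(X ≥ r | n = 112, p = 0.80) ≤ 0.05.
- r = 96 gives 0.0777, too large. r = 97 (97/112 = 86.6%) gives 0.0467.
- Power = P(X ≥ 97 | p = 0.90) = 0.9078.
- At n = 111, r is also 97 and power is 0.858. No smaller n reaches 90%.

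The stated >90% reproduces. The reserve is 5.0 − 4.7 = 0.3 points on type I error and 90.8 − 90 = 0.8 points on power. Under independence, Clopper–Pearson coverage is 97.5% at p = 0.90 and 96.8% at p = 0.80.

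**Step 2, the same rule with shared incidents.** Keep r = 97 and the unadjusted limits. Model each incident as beta-binomial with the given ICC and convolve over incidents to get the exact distribution of the total. The design effect is 1 + (Σm²/Σm − 1) × ICC, where m is the number registered at an incident. The denominator needed is approximated as 112 × design effect.

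For 42 singles and 35 pairs: Σm = 42 + 70 = 112 and Σm² = 42 + 140 = 182, so the design effect is 1 + 0.625 × ICC. At ICC 0.3 this is 1.19, and 112 × 1.1875 = 133.

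| Assumed registrants per incident | ICC | Type I error | Power | Coverage at 80% / 90% | n needed |
|---|---|---|---|---|---|
| 1.45 (42 singles, 35 pairs) | 0.1 | 5.2% | 90.1% | 96.2% / 97.0% | 119 |
| | 0.3 | 6.2% | 88.9% | 95.0% / 96.0% | 133 |
| | 0.5 | 7.2% | 87.8% | 93.8% / 94.9% | 147 |
| 2 (all pairs) | 0.1 | 5.5% | 89.7% | 95.9% / 96.7% | 124 |
| | 0.3 | 7.1% | 87.9% | 93.9% / 95.0% | 146 |
| | 0.5 | 8.7% | 86.3% | 91.9% / 93.2% | 168 |
| About 3 (36 triples, one four) | 0.1 | 6.3% | 88.8% | 94.9% / 95.9% | 135 |
| | 0.3 | 9.5% | 85.6% | 90.8% / 92.2% | 181 |
| | 0.5 | 12.3% | 83.1% | 86.7% / 88.3% | 226 |

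**Step 3, where the figures give way.** Type I error passes 5% and power falls below 90% at a design effect of about 1.04 to 1.08. With singles and pairs that is an ICC of roughly 0.06 to 0.12. At ICC 0.05 in that configuration the stated figures still hold (4.9% and 90.4%). Clopper–Pearson over-covers here, so coverage stays at or above 95% until the design effect is about 1.2 (true 80%) to 1.3 (true 90%).

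**Step 4, effect on the colour.** Table 3 assigns green at an observed 90% or more, which is 101 of 112. If true uptake is 80%, the chance of observing green is 0.3% under independence, 0.8% with singles and pairs at ICC 0.5, and 2.7% with about three per incident at ICC 0.5.

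**The case against.** **The article does not show that clustering is material.** It says that multiple registration is possible, not how often it happens, and it gives no correlation. A reader might infer that the stated error, power and coverage are simply wrong, or that 193 and 112 together prove clustering. Neither is supported. The >90% is correct under independence, and each denominator stands alone: 112 is just the smallest n reaching 90%, not a forecast of registrants from 77 incidents. This stands, and it limits the point to figures that are not assured.

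**The interval need not be too narrow.** Because Clopper–Pearson over-covers, mild clustering leaves coverage at or above 95%. This stands.

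**The progression decision barely moves.** The test's critical value of 86.6% lies in amber, a false green stays rare, the point estimate is not biased by clustering, and the article reads the proportions alongside qualitative and implementation data. This also stands and lowers the severity.

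**Linkage may be missing.** The app records the event, but Table 2 takes digital engagement from website analytics, a separate source. No section says each person's access is tied to an incident. The fix must allow for this.

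**The full protocol may deal with it.** Supplementary Appendix D is not shown. But the article itself names the test, denominator, power and interval, so the statement as published needs its condition.

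**Conclusion.** The point holds in a conditional form and is a should-fix. The article applies methods that need independence to a unit that its own registration process can nest within incidents, with no allowance and almost no reserve. With an assumed 1.45 registrants per incident (singles and pairs) and ICC 0.1 to 0.5, type I error is about 5.2–7.2%, power about 90–88%, and coverage at a true 80% about 96–94%. Larger shifts need larger clusters or higher correlation. If multiple registration proves rare, the effect is negligible. All of these sizes rest on assumed cluster sizes and ICCs; only the 4.7% and 90.8% follow from the article alone. The incident-level criterion with 193 incidents is not affected by bystander clustering.

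**What to change.** 1. Report website uptake with an incident-clustered 95% interval, using the app's event record as the cluster, and base the one-sided test on the same variance. One option is Clopper–Pearson on the effective sample size (112, or the actual denominator, divided by the estimated design effect), capped so that the interval is never narrower than the unadjusted one.
2. First confirm that website access can be linked to the event. If it cannot, give a sensitivity interval that applies a design effect built from the observed registrants per incident over a stated ICC range.
3. State that >90% power for 112 holds only if bystanders are independent.

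The pilot is complete and analysis is underway, so the number registered per incident should now be countable from the app and need not be assumed. The cost is a small amount of code, a sentence or two of text, and a slightly wider interval. As an illustration, 101 of 112 gives 83.1% to 95.0% unadjusted. With a design effect of 1.3125 (singles and pairs, ICC 0.5), the effective size is 112 / 1.3125 = 85.3 and the interval is 81.8% to 95.6%.

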### Data sharing and dissemination

Anonymised and aggregate findings will be disseminated through peer-reviewed publications, conference presentations, patient and public involvement groups, ambulance service governance meetings and cardiac arrest support networks. Data sharing beyond the study team will be limited to anonymised aggregate outputs where disclosure risk has been assessed. The full dataset will not be made publicly available because it may contain sensitive information relating to bystanders, OHCA events and support needs. Full protocol is available in Supplementary Appendix D.

## Discussion

RescQ™ is a structured UK initiative to provide real-time psychological support for OHCA bystanders, integrating prehospital engagement, a tailored digital platform, and professional LO follow-up to address a critical gap in the chain of survival: the wellbeing of those who step forward to assist in resuscitation.

The RescQ™ design evolved considerably from initial conception. Early plans centred on QR code wristbands distributed at scene, but collaboration with ambulance services and SCAUK highlighted limitations around inconsistent uptake and lack of ongoing support. This led to a digital-first solution embedded within ambulance clinician workflow, enabling on-scene registration, immediate access to resources, and personalised follow-up, strengthening both feasibility and scalability.

RescQ™ is fully integrated into ambulance clinician workflow, enabling immediate bystander registration at scene. Its digital-first approach allows rapid delivery of resources, avoiding delays inherent in traditional referral pathways. The self-referral mechanism to LOs ensures personalised, flexible support, allowing bystanders to engage on their own terms and timeline.

Existing international bystander support programmes typically rely on helpline self-referral or volunteer responder app registration, leaving gaps for those who do not initiate contact or are unregistered. By embedding RescQ™ directly into the prehospital process, the programme ensures all identified bystanders are offered support, regardless of prior registration or proactive engagement.

Anticipated challenges include inconsistent ambulance clinician compliance given the high-pressure nature of OHCA scenes, variable digital literacy among bystanders, and declining engagement over time. Additionally, appropriate referral thresholds must be maintained, balancing accessible LO support with timely escalation to specialist mental health services where needed.

If proven feasible, RescQ™ has potential impact beyond OHCA, including traumatic and natural disasters. At a community level, improved bystander experience may increase confidence and willingness to intervene in future arrests. At a systems level, findings could inform NHS strategies for integrating psychosocial care into emergency response, with broader national and international relevance given the widespread absence of structured rescuer follow-up.

### Limitations

As a feasibility study, RescQ™ is not powered to demonstrate clinical efficacy in improving psychological outcomes. Data are self-reported and may be affected by response bias. Uptake may be influenced by digital access, language, or cultural barriers, potentially limiting generalisability. The self-referral model may underrepresent those most severely affected, who are least likely to engage digitally. Follow-up is currently limited to short-term outcomes; longer-term psychological trajectories remain unknown.

## Conclusion

While primarily a feasibility study, RescQ™ will provide early insights into the scale of unmet need and the potential role of structured support for bystanders following cardiac arrest.

## Current status of project

At the time of submission, the 12-month pilot has been completed, and data analysis is underway.

## Ethical approval

The study has been reviewed by West of Scotland regional ethical committee (REC Ref: 24/WS/0088, IRAS ID 340729) and was classified as a service evaluation, meaning formal NHS REC and HRA approval is not required. It is conducted in compliance with NHS (national health service) research governance and General Data Protection Regulation (GDPR). Information governance and data protection frameworks were established in collaboration with pre-hospital and hospital information teams, ensuring secure data handling and storage.

## Use of AI technology

Generative AI was used to assist with the visual preparation of Fig. 4 in this manuscript. The figure was generated based on author-provided content. The originality, accuracy, and appropriateness of the figure were reviewed and confirmed by the authors, who take full responsibility for the submitted content.

## Availability of data and other materials

No new data was generated in this study.

